## **13. STATISTICAL CONSIDERATIONS**

### **13.1 Study Design/Endpoints**

This phase 1 trial will use a design involving four cohorts of patients with different degrees of liver dysfunction.

- The dose escalation rules used in this study are adapted from the standard up-and-down "3+3" design, and maintain the basic principles of that design. Normal, mild, moderate and severe liver dysfunction cohorts may be open concurrently. The design has been modified for this organ dysfunction study to eliminate waiting periods between dose levels as the clinical stability of patients with impaired hepatic function is frequently limited, and it is thus unreasonable to delay therapy for 2-3 weeks in this patient population. The disadvantage of this approach is that it may increase the number of patients who receive a dose that is subsequently found to be above the recommended dose level. However, the benefit is expected to outweigh this risk as this population of patients is small, has few or no standard therapeutic options, and these patients usually have a limited timeframe during which therapy can be safely administered.
- Although dose-finding will be carried out independently for each of the liver dysfunction groups, an ancillary constraint is imposed: accrual to Group D (severe) will occur one patient at a time (i.e., the second patient in a cohort will not be enrolled until the first patient completes cycle 1 and so on for each subsequent patient until the equivalent moderate dose is complete), and the dose recommended for a group with greater liver dysfunction cannot be greater than that for a group with a lesser dysfunction. While it is conceivable that patients with greater liver dysfunction might tolerate the study drug better than those with lesser dysfunction, it is considered very unlikely. Furthermore, the highest dose to be explored is no greater than the recommended dose for patients with normal liver function. Thus, the ancillary constraint can do no harm; it is intended to compensate in part for patient heterogeneity and yield more accurate final recommended doses than possible with independent dose escalation in the four liver dysfunction groups.

- At least 12 patients (1 per participating institution) will be entered into Group A (normal liver function). Patients in Group A are included in this study to obtain PK data in the same manner as for the patients with liver dysfunction. This group will also be followed for toxicity, but the definitions of recommended dose that are specific to patients with liver dysfunction will not be used.
- If a delay in completing one cohort occurs (*e.g.* severe liver dysfunction cohort has been completed enrollment), study data analysis and reporting will be considered for cohorts that have been completed. The enrollment for the remaining cohorts will continue concomitantly to data analysis.
- Toxicity will be graded according to the NCI CTCAE v4.0.0 and relationship to the study drug; results will be tabulated by liver dysfunction group. All patients who receive any amount of trametinib will be evaluable for toxicity, but patients who receive other than the prescribed dose and do not experience a DLT will be considered inevaluable for DLT. Patients who are not evaluable for DLT will be replaced. One exception is made for patients enrolled in the severe hepatic dysfunction cohort (Group D). As patients with severe hepatic dysfunction can deteriorate quickly due to their disease and poor organ functions, patients in this cohort who complete PK schedule at day 16 will be considered evaluable for DLT assessment.

Primary Endpoints:

- To provide appropriate dosing recommendations for patients with varying degree of hepatic dysfunction receiving trametinib (mild, moderate and severe).
- To establish the maximum tolerated dose (MTD) and dose-limiting toxicity (DLT) of trametinib in advanced cancer patients with varying degrees of hepatic dysfunction
- To characterize the PK profile of trametinib in advanced cancer patients with varying degrees of hepatic dysfunction.

Secondary Endpoints:

- To document the non-DLTs associated with the administration of trametinib in patients with varying degrees of hepatic dysfunction.
- To document any antitumor activity associated with trametinib treatment of patients enrolled on this study.
- To explore and characterize predictive biomarkers for individual cancer patients utilizing genomic sequencing technologies.

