### 5.3.2 Non-Hematologic toxicity:

- Allergic reaction/hypersensitivity will not be considered dose-limiting
- Alopecia will not be considered dose limiting
- Any Grade 4 non-hematologic toxicity
- Grade 3 non-hematologic toxicity (except nausea, vomiting or diarrhea that can be controlled by appropriate medical intervention or prophylaxis and that resolves to Grade 1 within 48 hours with medical intervention or electrolyte toxicities unable to

be corrected to  $\leq$  Grade 1 or baseline within 48 hours) excluding specific toxicities (\* see below)

- Treatment-related toxicities that result in failure to receive  $\geq 75\%$  of trametinib doses in cycle 1 despite maximal supportive care measures
- Delays in starting cycle 2 by  $\geq 2$  weeks due to treatment-related toxicity will constitute a DLT

\* **Liver toxicity:** Worsening liver function, as defined by a rise in serum bilirubin, not related to tumor progression or stent occlusion will constitute a DLT if:

- For patients in the Hepatic Dysfunction cohorts (B, C, D):

Mild group (B): progresses into severe dysfunction range for 1 week or longer.

Moderate group (C): bilirubin increases from baseline  $\geq 3$  fold for 1 week or longer.

Severe group (D): bilirubin increases from baseline  $\geq 2$  fold for 1 week or longer.

*Note:* Patients requiring stent placement during study treatment will be allowed to continue study treatment after stent placement and a period of stabilization of clinical status and liver function tests. Two measurements at least 2 days apart will be accepted as evidence of stable hepatic function.

\* **Cardiac related toxicity:** symptomatic cardiac failure;  $\geq$  grade 3 LV systolic dysfunction reduction in LVEF  $\geq 10$  points from baseline and below the institution's lower limit of normal, without improvement within 2 weeks; QTc > 500 msec; other  $\geq$  grade 3 cardiac disorders.

Management and dose modifications associated with the above adverse events are outlined in Section 6.

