| CTCAE v4.0 Grade                                                                                                                                                                                                                                                                                                                                 | Management Guideline                                                                          | Dose Modification                                                                                                                                                                                                                                                                                                                                                                |
| Grade 1                                                                                                                                                                                                                                                                                                                                          | Monitor as clinically indicated. Provide supportive care according to institutional standards | Continue trametinib at current dose level.                                                                                                                                                                                                                                                                                                                                       |
| Grade 2 (tolerable)                                                                                                                                                                                                                                                                                                                              |                                                                                               | 

• Interrupt treatment until resolution to grade 1 or baseline.

• Upon resolution, restart treatment at current dose level.

                                                                                                                                                                                               |

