| Grade 2 (intolerable) and Grade 3                                                                                                                                                                                                                                                                                                                |                                                                                               | 

• Interrupt treatment until resolution to grade 1 or baseline.

• Upon resolution to baseline or grade 1, restart with one level of dose reduction

• If the Grade 3 toxicity recurs, interrupt trametinib; When toxicity resolves to Grade 1 or baseline, restart trametinib reduced by another dose level

 |
| Grade 4                                                                                                                                                                                                                                                                                                                                          |                                                                                               | If the event resolves to grade 1 or baseline discuss potential continuation of trametinib with Medical Monitor; if continuation of treatment agreed then restart trametinib at dose reduced by one dose level .
If the event does not resolve, permanently discontinue trametinib.                                                                                     |
| Trametinib should be discontinued if treatment delay is ≥21 days due to toxicities. If the investigator concludes that continued trametinib will benefit a patient, the study chair and CTEP Medical Monitor may be consulted for the possibility of resuming trametinib, provided that toxicities have resolved to baseline or grade 1.         |                                                                                               |                                                                                                                                                                                                                                                                                                                                                                                  |

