| Grade 2                                                                                                                                                                                                                                                                                                                                                                                                                                      | 
 
• Initiate prophylactic and symptomatic treatment measures.
 
• Use moderate strength topical steroid.
 
• Reassess after 2 weeks.
 
 | 
 
• Reduce trametinib by one dose level.
 
• If rash recovers to ≤ grade 1 within 2 weeks, increase dose to previous dose level.
 
• If no recovery to ≤ grade 1 within 2 weeks, interrupt trametinib until recovery to ≤ grade 1.
 
• Restart trametinib at reduced dose level.
 
 |
| Grade ≥3                                                                                                                                                                                                                                                                                                                                                                                                                                     | 
 
• Use moderate strength topical steroids PLUS oral methyl-prednisolone dose pack.
 
• Consult dermatologist.
 
                                          | 
 
• Interrupt trametinib until rash recovers to ≤ grade 1.
 
• Restart with trametinib reduced by one dose level.
 
• If no recovery to ≤ grade 2 within 4 weeks, permanently discontinue trametinib.
 
                                                                                 |

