| Uncomplicated Diarrhea,
Grade 1 or 2         | 
 
• Diet: Stop all lactose containing products; eat small meals, BRAT-diet (banana, rice, apples, toast) recommended.
 
• Hydration: 8-10 large glasses of clear liquids per day (e.g., Gatorade or broth).
 
• Loperamide: Initially 4 mg, followed by 2 mg every 4 hours or after every unformed stool; maximum 16 mg/day. Continue until diarrhea-free for 12 hours.
 
• Diarrhea >24 hours: Loperamide 2 mg every 2 hours; maximum 16 mg/day. Consider adding oral antibiotics.
 
• Diarrhea >48 hours: Loperamide 2 mg every 2 hours; maximum 16 mg/day. Add budesonide or other second-line therapies (otretotide, or tincture of opium) and oral antibiotics.
 
 | 
 
• Continue trametinib.
 
• If diarrhea is grade 2 for > 48 h, interrupt trametinib until diarrhea resolves to grade ≤1.
 
• Restart trametinib at the same dose level
 
• If treatment delay is >21 days, discontinue trametinib.
 
 |

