**For patients in the Mild hepatic function (B):**

- Liver chemistry stopping criteria are as follows:
  - If bilirubin  $> 3$ X ULN any time, hold trametinib. Treatment may resume under the following conditions:
    - The bilirubin returns to the range of mild dysfunction within 2 weeks. The patient will be treated at one dose level lower unless they are already dose reduced, in which case they will be taken off treatment.
    - If bilirubin does not return to treatable range within 2 weeks, patient will be off trametinib.

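### Section 13.1 does not exempt holds or reductions ordered by Section 6, so Group B and C patients with tolerated cycle 1 toxicity may be dropped from the DLT count and replaced

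*Protocol*

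**What the plan says.** Section 13.1 sets the evaluability rule for DLT: "patients who receive other than the prescribed dose and do not experience a DLT will be considered inevaluable for DLT". Inevaluable patients are replaced. The single exception is Group D, where completing the PK schedule at day 16 is enough. Group A falls outside the DLT definitions (5.1.1), so the strict rule applies to Groups B and C.

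Section 5.3.2 has its own missed-dose criterion. It counts a DLT when treatment-related toxicity means the patient fails to receive at least 75% "of trametinib doses in cycle 1 despite maximal supportive care measures". For bilirubin in Group B, the DLT is: "Mild group (B): progresses into severe dysfunction range for 1 week or longer".

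Section 6 orders changes for events below those thresholds:

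- Table 12, tolerable Grade 2 event: "Interrupt treatment until resolution to grade 1 or baseline", then resume at the same level.
- Table 12, intolerable Grade 2 event: interrupt, then "restart with one level of dose reduction".
- Table 15, Grade 2 diarrhea lasting over 48 hours: "interrupt trametinib until diarrhea resolves to grade" 1 or lower.
- Table 13, Grade 2 rash: "Reduce trametinib by one dose level".
- Section 6.1.5, Group B, bilirubin above 3 times "ULN any time, hold trametinib"; if treatment resumes, it is one level lower.

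Section 13.3 recommends the highest dose with at most 1 DLT in 6 patients.

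**The concern.** The two rules do not meet. A patient can follow the protocol exactly, have a dose held or lowered on its instruction, finish cycle 1 without a DLT, and still be classed as not having received the prescribed dose. That patient tolerated the assigned dose by the protocol's own DLT definition, yet leaves the denominator.

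Removal then depends on outcome. A patient with a DLT always stays; a patient with lesser toxicity goes and is replaced by someone who may have a DLT. The observed DLT rate is pushed upward, and an acceptable dose is more likely to be rejected. A lower dose in Group B would carry further, because 13.1 bars a more impaired group from a higher recommended dose than a less impaired one. Replacements also use scarce patients.

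**Working it through.** **The gap between the two rules.** Cycle 1 has 28 daily doses, and 0.75 × 28 = 21. Receiving 21/28 = 75.0% is not a DLT on this ground; 20/28 = 71.4% is, if toxicity-related. So 1 to 7 missed doses are tolerated by 5.3.2.

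**Who is dropped depends on what the phrase in 13.1 means.**

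| Reading of prescribed dose | Held 1 to 7 doses, no DLT | Reduced in cycle 1, no DLT |
|---|---|---|
| Every assigned dose taken (literal) | Dropped | Dropped |
| Assigned mg level only | Kept | Dropped |
| Dosing as Section 6 directs | Kept | Kept |

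**Effect where patients are dropped.** Let p be the true DLT rate and q the share of all patients who are DLT-free but held or reduced. Neither is given in the protocol; both are assumptions. Among evaluable patients the DLT rate is r = p/(1 − q).

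Probability of failing the at-most-1-of-6 rule (13.3), which governs Group B at 2 mg: 1 − [(1 − r)^6 + 6r(1 − r)^5].

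Probability of not clearing a level under the 3+3 escalation rule (Table 10), as for Group C at 1.5 mg: 1 − [(1 − r)^3 + 3r(1 − r)^5].

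| p | q | r | Fails 1-of-6 | Fails escalation |
|---|---|---|---|---|
| 20% | 0 | 20.0% | 34% | 29% |
| 20% | 5% | 21.1% | 37% | 31% |
| 20% | 10% | 22.2% | 40% | 34% |
| 20% | 20% | 25.0% | 47% | 40% |
| 10% | 0 | 10.0% | 11% | 9% |
| 10% | 5% | 10.5% | 12% | 10% |
| 10% | 10% | 11.1% | 14% | 11% |
| 10% | 20% | 12.5% | 17% | 14% |

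If q is instead the share of DLT-free patients, then r = p/[p + (1 − p)(1 − q)]. At p = 20% and q = 20%, r = 0.20/0.84 = 23.8%, and the 1-of-6 failure probability is 44% rather than 47%.

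**Replacements.** Six evaluable patients require 6/(1 − q) treated: 6.3, 6.7 and 7.5 at q = 5%, 10% and 20%.

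**Example, Group B at 2 mg.** Six are treated. One has a DLT, and another misses 3 doses for Grade 2 diarrhea (25/28 = 89%). Counting all six gives 1/6, and 2 mg is recommended. Under the literal rule the count is 1/5 and another evaluable patient is needed. At p = 20% that next evaluable patient has a DLT with probability r, between 21% and 25% for q of 5% to 20%. A DLT there makes 2/6, and 2 mg fails.

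**The case against.** The strongest reply is that the strict reading is only an inference. Section 13.1 does not mention missed or held doses. Table 7 lists dose and schedule in separate columns, so a patient assigned 2 mg who takes 2 mg on 25 days arguably received the prescribed dose. Prescribed could also mean dosed as the protocol directs, and then an ordered hold or reduction is compliant. Elsewhere the protocol plainly expects some missed doses: Section 6 does not make up doses lost to delays, and Section 8.1 limits when a late dose may be taken. The Group D exception is justified by rapid deterioration, so it says little about a patient who misses three doses and reaches day 28.

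Much of this stands. A reader might infer that such patients are removed on any reading, or that a single missed dose certainly disqualifies. The documents do not support either. But no section adopts a benign reading, and the mg-level reading still drops a patient reduced in cycle 1. Section 5.3 speaks of individual reductions in later cycles, so how often that happens in cycle 1 is unclear; Tables 12 and 13 and Section 6.1.5 carry no such limit.

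It is also fair that requiring full exposure before clearing a dose is defensible for a drug that accumulates, and that dose decisions need Principal Investigator sign-off (12.1). Sign-off does not say which patients count.

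**Conclusion.** The point holds as an unresolved rule with a one-sided effect. On two of three plausible readings, some Group B or C patients with tolerated toxicity are dropped by outcome, which biases the DLT rate upward and the recommended dose downward.

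The size depends wholly on q. The background section shows that rash and diarrhea are common at 2 mg, but it gives no rate of cycle 1 holds or reductions. At an assumed p of 20%, the effect is small at q = 5% (34% to 37%) and material only near q = 20% (47%, or 44% with q taken among DLT-free patients). A reader might infer that the rule endangers patients or conceals toxicity; it does not. The bias is conservative and every DLT is counted. This is a cheap improvement to a rule already stated in the protocol, which drives decisions during escalation.

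**What to change.** Amend 13.1 for Groups B and C:

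- A patient is DLT-evaluable with a cycle 1 DLT, or if followed to day 28 with at least 75% of assigned cycle 1 doses taken (21 of 28).
- Holds or reductions ordered by Section 6 for toxicity short of a DLT do not by themselves make a patient inevaluable. Say explicitly that doses taken at a level so reduced count as taken.
- Replace only patients below 75% for reasons other than related toxicity; below 75% for related toxicity is already a DLT.
- Tabulate cycle 1 holds and reductions by dose level beside the DLTs.

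The cost is three or four sentences, with no new data and, where patients would have been dropped, fewer replacements. The downside is that some counted non-DLT patients will have had up to 25% fewer doses, or some reduced doses, so toxicity at full dose could be slightly understated. With the effective half-life of about 4.5 days in Section 2.2.1.2, concentration falls to 2^(−3/4.5) = 63% after a 3-day hold and 2^(−7/4.5) = 34% after a 7-day hold. Section 5.3.2 already accepts that many missed doses without calling a DLT, and the tabulation lets those deciding on dose see it.

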## Dose Escalation Schema

Dose escalation will proceed within each cohort according to the following schema (Table 9).

**Table 9:** Dose escalation schema for each cohort as defined by hepatic function.

|            | Group A                 | Group B                  | Group C                      | Group D                    |
|------------|-------------------------|--------------------------|------------------------------|----------------------------|
|            | Normal hepatic function | Mild hepatic dysfunction | Moderate hepatic dysfunction | Severe hepatic dysfunction |
| Dose Level | mg                      | mg                       | mg                           | mg                         |
| Level - 2  | -                       | 1                        | 0.5                          | -                          |
| Level - 1  | -                       | 1.5                      | 1                            | 0.5                        |
| Level 1    | 2                       | 2                        | 1.5                          | 1                          |
| Level +1   | no escalation           | no escalation            | 2                            | 1.5                        |
| Level +2   | no escalation           | no escalation            | no escalation                | 2                          |

Dose-limiting toxicity (DLT) is defined above (Sections 5.3.1. and 5.3.2).

The patient's starting dose will be assigned by the Central Office Study Coordinator at the time of registration. The patients' hepatic dysfunction group may be altered after registration if hepatic function tests performed within 24 hours of commencing trametinib have changed from registration results as described in section 5.1.1. The dose may be reduced for individual patients in subsequent cycles depending on toxicity as outlined in section 6.

Normal, mild, moderate and severe liver dysfunction cohorts may be open concurrently.

The initial cohorts of patients will begin on dose level 1 based on their level of hepatic dysfunction. Liver function tests (AST and total bilirubin) should be repeated within 24 hours prior to starting treatment on study to determine hepatic dysfunction cohort.

Escalation is planned as the standard "3+3" schema, for each hepatic dysfunction cohort (Cohorts B, C and D), with the exception of the normal hepatic function cohort (Cohort A) (Table 10).

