## 9. BIOMARKER, CORRELATIVE, AND SPECIAL STUDIES

### 9.1 Pharmacokinetic Studies

Pharmacokinetic studies will be performed on all enrolled patients to assess the bio-distribution of trametinib in patients with organ dysfunction. At the Principal Investigator’s discretion, this requirement may be waived in case of patient hardship, including lack of venous access. In this event, patients will be replaced to ensure that

adequate PK data are obtained for each group (i.e., at least 3 patients per group and at least 6 patients at the MTD level).

In blood, trametinib has been shown to be the predominant radio- component and M5 the only detectable minor component (<7% of the blood radioactivity). Plasma concentrations will be measured by Covance Laboratory Inc using a validated LC/MS/MS assay. All PK measurements for this study will be performed at Covance Laboratory Inc. All data and results will be made available to the investigators on this study and to CTEP. The minimum turnaround time for PK measurements will be 4 weeks from receipt of samples by the analytical laboratory. In patients who experience unexpected serious toxicity efforts will be made to have analysis available in 2 weeks. Availability of PK data is anticipated prior to dose escalation to another dose level.

PK sampling will be performed in cycle 1 for all patients. In patients with incomplete PK from cycle 1 and in those who change dose level or hepatic dysfunction group between cycles, repeat PK sampling is encouraged in subsequent cycles but is not mandatory. For severe liver dysfunction cohort, patients who complete PK schedule at day 16 will be considered evaluable for DLT assessment.

Specimen Collection and Analysis Details are provided in the “Pharmacokinetic Laboratory Manual” supplied by the Coordinating Central Office. Note: This will be disseminated with the clinical protocol and is also available to investigators on request from the coordinating center.

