### **12.1 Study Oversight**

This protocol is monitored at several levels, as described in this section. The Protocol Principal Investigator is responsible for monitoring the conduct and progress of the clinical trial, including the ongoing review of accrual, patient-specific clinical and laboratory data, and routine and serious adverse events; reporting of expedited adverse events; and accumulation of reported adverse events from other trials testing the same drug(s). The Protocol Principal Investigator and statistician have access to the data at all times through the CTMS web-based reporting portal.

For the Phase 1 portion of this study, all decisions regarding dose escalation/expansion/de-escalation require sign-off by the Protocol Principal Investigator through the CTMS/IWRS. In addition, for the Phase 1 portion, the Protocol Principal Investigator will have at least monthly, or more frequently, conference calls with the Study Investigators and the CTEP Medical Officer(s) to review accrual, progress, and adverse events and unanticipated problems.

All Study Investigators at participating sites who register/enroll patients on a given protocol are responsible for timely submission of data via Medidata Rave and timely reporting of adverse events for that particular study. This includes timely review of data collected on the electronic CRFs submitted via Medidata Rave.

All studies are also reviewed in accordance with the enrolling institution's data safety monitoring plan.

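### The Group D Day 16 exception has no dose condition, so a patient dose-reduced before Day 16 without a DLT counts as DLT-free at the assigned level

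*Protocol*

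**What the plan says.** **Evaluability.** Section 13.1 states the general rule: "patients who receive other than the prescribed dose and do not experience a DLT will be considered inevaluable for DLT", and such patients are replaced. The Group D exception follows directly: "patients in this cohort who complete PK schedule at day 16 will be considered evaluable for DLT assessment". Section 9.1 repeats it: "For severe liver dysfunction cohort, patients who complete PK schedule at day 16 will be considered evaluable for DLT assessment". The reason given in Section 13.1 is that these patients can worsen quickly from their disease and poor organ function. The DLT window in Section 5.3 is otherwise the first 28 days.

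**Dose reduction without a DLT.** The opening of Section 6 lets reductions be considered for toxicity short of a DLT, but only after the Principal Investigator is consulted. For Grade 2 rash, Table 13 (Section 6.1.2) says "Reduce trametinib by one dose level", with a return to the previous level if the rash settles within 2 weeks. For intolerable Grade 2 toxicity, Table 12 (Section 6.1.1) calls for an interruption and then "Upon resolution to baseline or grade 1, restart with one level of dose reduction". The Dose Escalation Schema says "The dose may be reduced for individual patients in subsequent cycles depending on toxicity as outlined in section 6".

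**Missed doses.** Under Section 5.3.2, related toxicity that leaves the patient short of 75% "of trametinib doses in cycle 1 despite maximal supportive care measures" is itself a DLT.

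**The concern.** The exception is attached to the off-dose rule. Read literally, it lifts that rule for every Group D patient who completes the Day 15 to 16 sampling, whatever dose was being taken. Rapid deterioration justifies accepting about 16 days of observation in place of 28. It does not justify crediting a level that the patient had already left.

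Take a Group D patient who starts at 1 mg, is cut to 0.5 mg before Day 15 for Grade 2 rash, and is then sampled. This patient enters the Table 10 count as DLT-free at 1 mg. The same history in Group B or C would lead to replacement. Where the crediting changes a decision, it does so toward passing the level, in the cohort that the protocol otherwise protects with one-at-a-time accrual. The same count feeds the recommended-dose rule in Section 13.3 (at most 1 DLT in 6), and dose recommendations are a primary objective.

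**Working it through.** The protocol gives no figure that depends on this wording, so there is none to reproduce. The check has two parts.

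**1. Does the protocol leave the route open?**

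- *Timing of reductions.* The Dose Escalation Schema speaks of later cycles, and Section 9.1 mentions patients who change dose level between cycles. Neither forbids a reduction in cycle 1, and Tables 12 and 13 are not limited to later cycles.
- *The 75% rule.* 75% of 28 doses is 21, so up to 28 − 21 = 7 missed doses is not a DLT. A Grade 2 rash reduction starts without an interruption, so no dose need be missed. An interruption of up to 7 doses followed by a lower dose also stays within the limit.
- *Size of the cut in Group D (Table 8).* One level down is 1 to 0.5 mg (50%), 1.5 to 1 mg (33%) or 2 to 1.5 mg (25%). Section 6 allows nothing below 0.5 mg.

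The route is open but narrow.

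**2. How much could it matter?**

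Assumed inputs, none of them in the protocol: true DLT risk p at the level, share r of patients reduced before Day 16 without a DLT, and the reduced patient's remaining DLT risk (p/2, or 0 as the upper bound). A level passes Table 10 with 0 DLTs in 3, or with 1 in 3 followed by 0 in 3.

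*Unconditional.* The per-patient risk as counted is p′ = (1 − r)p + r × (remaining risk), and

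P(pass) = (1 − p′)³ + 3p′(1 − p′)⁵.

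At p = 0.30 with replacement: 0.343 + 0.9 × 0.16807 = 0.494.

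| r (assumed) | p′, half risk | P(pass) | p′, no risk | P(pass) |
|---|---|---|---|---|
| 0.05 | 0.2925 | 0.510 | 0.285 | 0.525 |
| 0.10 | 0.285 | 0.525 | 0.27 | 0.557 |
| 0.20 | 0.27 | 0.557 | 0.24 | 0.622 |

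The chance that at least one of the first three is such a patient is 1 − (1 − r)³: 0.143, 0.271 and 0.488.

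*Conditional on exactly one such patient among the first three.* With remaining risk s in that slot,

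P(pass) = (1 − p)²(1 − s) + [2p(1 − p)(1 − s) + s(1 − p)²](1 − p)³.

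| p | Replaced (s = p) | Counted, s = p/2 | Counted, s = 0 |
|---|---|---|---|
| 0.20 | 0.709 | 0.756 | 0.804 |
| 0.30 | 0.494 | 0.564 | 0.634 |
| 0.40 | 0.309 | 0.386 | 0.464 |

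*Simplifications.* Patients are independent, and a replacement carries risk p. Under the general rule a reduced patient who then has a DLT still counts, so the replaced figure is slightly high in the half-risk case.

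**The case against.** The strongest reply is that the exception explains itself. It is for patients who deteriorate, so its natural sense is a shorter window, and nowhere does the protocol say that a dose-reduced patient is DLT-free at the assigned level. A reader might infer that the protocol means to credit such patients. The text does not support that inference. What stands is that the only written condition is PK completion, so the intent has to be guessed.

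Other points limit the reach, and they stand:

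- Two places describe dose changes as happening in or between later cycles.
- Grade 3 non-hematologic toxicity is mostly a DLT already, which leaves mainly Grade 2 events. A rash reduction may be reversed within 2 weeks.
- In the phase 3 melanoma trial (Section 2.2.1.3), median onset of skin toxicity was 15 days, so about half of those onsets came later than that. That trial used 2 mg, and Group D starts at 1 mg.
- The Principal Investigator is consulted on non-DLT reductions, and under Section 12.1 "all decisions regarding dose escalation/expansion/de-escalation require sign-off by the Protocol Principal Investigator". That role should know of the reduction. The rule being applied still calls the patient evaluable.
- Group D doses may not go beyond those being tested in less severe cohorts, and its recommended dose may not exceed that of Group C, which has no Day 16 exception. At least 6 patients are needed at the recommended dose, and PK data are expected before escalation. These bound the harm but do not correct the count.

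Replacement has a bias of its own. It removes a patient who tolerated the dose poorly, and the calculation, which gives replacements the level's own risk, cannot show this. The fix brings Group D into line with Groups B and C. It does not make the count bias-free.

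**Conclusion.** The point holds as a gap in wording with a one-sided effect. The exception is broader than its stated reason, and followed literally it credits a Group D patient as DLT-free at a level not held through the Day 16 sample.

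The likely size is modest. At an assumed true DLT risk of 30%, with an assumed 5% to 10% of patients reduced and half the risk remaining, the chance of passing a level rises from 49% to about 51% to 53%, or 2 to 4 percentage points. With no residual risk it is at most 53% to 56%. The zero-risk bound is unlikely to be reached, because the patient has already had toxicity at the full dose.

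Two stronger readings are tempting. One takes the conditional rise from 49% to as much as 63% as the expected effect. That rise applies only where such a patient is among the first three, and the protocol gives no frequency. The other takes halving of the dose as the usual case, but it arises only from 1 mg. Nor is the shortened window itself at fault here. The change is worth making because it is cheap and protects the cohort with the least hepatic reserve.

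**What to change.** Add to Sections 9.1 and 13.1: the Day 16 exception applies only to Group D patients who remained at the assigned dose level through the Day 16 sample; a Group D patient dose-reduced earlier without a DLT is not evaluable at that level and is replaced.

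This keeps the shorter window for patients who deteriorate and leaves the dose-modification rules in Section 6 unchanged. The cost is one sentence in each of two sections and an occasional extra Group D patient, as Section 13.1 already requires in Groups B and C. Each replacement can be slow, because Group D may be accruing one patient at a time.
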